**Methods:**

This prospective, single-center, randomized controlled, pilot trial will recruit 60 AMI patients scheduled for PCI at the Yueyang Hospital of Integrated Traditional Chinese and Western Medicine, China. The patients will be randomized in a 1:1 ratio into the EA or the control groups. Patients in the control group will undergo standard PCI. Patients in the EA group will undergo intraoperative electroacupuncture while undergoing standard PCI. Incidence of SF-NR is the primary outcome for this study. This study will also assess secondary outcomes including cardiac biomarkers, inflammatory biomarkers, pain and anxiety scores, electrocardiography parameters, traditional Chinese medicine (TCM) symptom score, and major adverse cardiovascular and cerebrovascular events (MACCE). All the included patients will undergo laboratory tests including routine blood tests, levels of electrolytes, as well as liver and renal function tests. Patients will be followed up for 1 month after the procedure.

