#### Secondary outcomes

2.9.2

(1)*Cardiac biomarkers*: Assessments of serum high-sensitive cardiac troponin I (cTnI), myoglobin (Myo), creatine kinase-MB (CK-MB), and N-terminal pro-brain natriuretic peptide (NT-proBNP).(2)*Inflammatory biomarkers*: Assessments of leukocytes, neutrophils, lymphocytes, and high-sensitivity C-reactive protein (Hs-CRP).(3)*Chest pain score*: Chest pain severity will be assessed using the Numeric Rating Scale (NRS) with the participants rating pain on a 10-point scale, where 0 represents no pain, 1–3 indicates mild pain, 4–6 moderate pain, and 7–10 indicates severe pain.(4)*Anxiety score*: This will be evaluated using the Visual Analogue Scale for Anxiety (VAS-A) with 10-point scoring system where 0 indicates no anxiety, 1–3 indicates mild anxiety, 4–6 indicates moderate anxiety, and 7–10 indicates severe anxiety.(5)*Electrocardiogram examination*: Assessment of cardiac activity using the electrocardiograms.(6)*TCM symptom score*: Symptom severity grading will be based on the 2002 Guidance principle of clinical research on new drugs of Traditional Chinese Medicine (46). The severity grading categories are none, mild, moderate, and severe. Major symptoms will be scored as 0, 3, 6, or 9 points. The secondary symptoms will be scored as 0, 1, 2, or 3 points. The specific scores are shown in the Supplementary Material. TCM symptom score = major symptoms score + secondary symptoms score. The efficacy index will be calculated using the following formula: [(Score at initial admission - Score at 24 h after PCI)/Score at initial admission] × 100%. The efficacy index is classified into the following three grades: ineffective (0%–30%), effective (30%–70%), and significant (70%–100%). Total effective rate = significant effective rate + effective rate.(7)*MACCE*: The incidences of major adverse cardiovascular and cerebrovascular events (MACCE) include hemorrhage, recurrent myocardial infarction, revascularization, readmission, and cardiogenic death during the follow up within one month after PCI.

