### Adverse events

2.11

Adverse events (AEs) are unexpected symptoms, signs, or health conditions associated with the treatment. Pre-existing health conditions or diseases will be categorized as AEs only if they worsen post-treatment. Abnormal laboratory tests will be considered as AEs if they represent clinically significant symptoms that require treatment. Common adverse reactions to electroacupuncture include broken needles, fainting, bleeding, bruising, infection, swelling, and other discomforts following needle insertion such as post-acupuncture pain, nausea, palpitations, dizziness, headache, and insomnia. Detailed AE data will describe the symptoms, severity, onset date, relationship with study manipulation, measures taken in response (including drug combination, dosage, start and end times), intervention methods (such as ceasing acupuncture), duration, follow-up, and outcomes. Follow-up will be conducted immediately after enrolment, and timely reports will be submitted to the principal investigator until all the issues are resolved. The investigator has the authority to determine trial termination and provide economic compensation for study-related harm. Loss of follow-up will also be recorded if the investigator cannot obtain information regarding adverse events.

Serious Adverse Events (e.g., resulting in death, hospitalization, or disability) will be promptly reported to the principal investigator and the Medical Ethics Committee. The Case Report Form (CRF) will document the time of death and autopsy results, if applicable.

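### MACCE is named for cerebrovascular events but lists no stroke, and the AE definition conflicts with its own section, so relevant events can go uncounted

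*Protocol article*

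**What the plan says.** MACCE is a secondary outcome (Abstract, Methods; section 2.9.2, item 7). The name covers both cardiovascular and cerebrovascular events, and the components follow it: "The incidences of major adverse cardiovascular and cerebrovascular events (MACCE) include hemorrhage, recurrent myocardial infarction, revascularization, readmission, and cardiogenic death", counted over a window of one month from the procedure. Table 1 schedules MACCE at one month only.

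Section 2.11 opens with the definition "Adverse events (AEs) are unexpected symptoms, signs, or health conditions associated with the treatment". The same section then says "Common adverse reactions to electroacupuncture include broken needles, fainting, bleeding, bruising, infection, swelling", followed by further reactions, and sets out what is recorded for each event: "Detailed AE data will describe the symptoms, severity, onset date, relationship with study manipulation", among other items. Table 1 schedules adverse events at every timepoint. Section 2.11 also has serious adverse events reported to the principal investigator and the ethics committee.

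Section 2.10 bases the safety assessment on laboratory tests at admission and three days after the procedure. The Discussion adds that adverse events will be evaluated when the trial is complete.

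**The concern.** Both passages are counting rules, and each, if followed as worded, leaves out events that its own heading or section appears to want.

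For MACCE, a reader of the results will take the label at face value and assume that strokes were counted. They have no component of their own. Meanwhile two of the five components, hemorrhage and readmission, are not tied to the kind of event the label describes. The composite may therefore consist partly of events that EA is not expected to change, which blurs any real difference.

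For AEs, the definition sets two conditions for an event to be captured at all: it must be unexpected and it must be treatment-associated. In a pilot meant to inform later trials, incomplete AE capture would carry forward into what is believed about the safety of needling during PCI.

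**Working it through.** The article gives no rate for MACCE or AEs, so there is no figure to reproduce. The check sets the passages side by side.

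**1. MACCE: name against list.** Where could an ischemic stroke within one month be counted?
- Hemorrhage: no. It might take in an intracranial bleed, but not an ischemic stroke.
- Recurrent myocardial infarction: no.
- Revascularization: not as a stroke.
- Readmission: only if the stroke happens after discharge and leads to a readmission. A stroke during the index stay is not a readmission.
- Cardiogenic death: no. A fatal stroke is not a cardiac death.

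So of the five listed components, one offers an indirect route and none names a cerebrovascular event.

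**2. MACCE: components without a stated link to the label.** Hemorrhage and readmission appear with no tie to a major cardiovascular or cerebrovascular event. The same definition and one-month window apply to both arms. Events unrelated to treatment then add to both arms alike and pull the ratio of the two composite risks towards 1. This is dilution, not a shift in favor of one arm.

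**3. AEs: definition against its own section.** Cross the two conditions in the opening sentence of section 2.11.

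| | Treatment-associated | Not treatment-associated |
|---|---|---|
| Unexpected | captured | dropped |
| Expected | dropped | dropped |

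Read literally, one cell in four is captured. Two statements in the same section do not fit that:
- The listed common EA reactions are by nature expected, so they fall in a dropped cell, yet the section plainly treats them as relevant.
- Relationship is recorded for each AE. If association is already required for an event to be an AE, that field can at most grade the association. It cannot record an unrelated event.

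**4. Consequence for comparing AE rates.** Expected needle reactions can occur only in the EA arm, so a literal reading would lower the EA count. The association condition asks someone to judge cause before an event is recorded, and section 2.7 says that participants and acupuncturists know the allocation. The article does not say which treatment the definition means. The direction of any net error is therefore not established. What follows is that AE rates may be incomplete and that their comparison is not reliable.

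**The case against.** **The wording is loose, not operative.** *Include* may introduce examples only, and *unexpected* may stand for *untoward*: section 2.11 lists needle reactions and provides for stopping acupuncture in response, so capture seems intended. This is a fair reading of intent. But a non-exhaustive list leaves the composite open-ended, and a definition that works only when its key adjective is ignored still needs rewording.

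**Missed events have another route.** Serious adverse events are reported with no stated limit by arm, so a disabling stroke or a non-cardiac death should surface there. That largely stands, and it lowers the severity. It does not put the event into MACCE, and serious AEs are normally a subset of AEs, so the narrow definition could restrict this route too.

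**Stronger readings that a reader might infer, and that the article does not support:**
- *MACCE is biased between arms, because needle-site bleeding counts as hemorrhage in the EA arm.* One definition and one window apply to both arms, and section 2.14 says that efficacy and safety assessors are unaware of allocation. Needle bleeding is listed in the AE section, and nothing directs it to MACCE. Both arms also have arterial access, heparin and antiplatelet drugs.
- *Control patients cannot have AEs.* The heading of section 2.8.1 itself calls standard PCI a treatment, and Table 1 schedules AEs at all timepoints without limit by arm.
- *Planned staged procedures will swamp the composite.* The article does not mention staged PCI. Bleeding grades and rules on planned events are details that an article may leave to the full protocol.
- *Counting only cardiac death is an error.* It is a design choice, though one that is best accompanied by all-cause death.

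**Conclusion.** Wrong as written, minor severity. Two contradictions stand on the text alone: a cerebrovascular label with no cerebrovascular component, and an AE definition limited to unexpected, treatment-associated conditions beside a list of expected reactions and a separate relationship field. The first leaves ischemic stroke without a place of its own, and the loosely tied components can dilute the composite in both arms. The second can make AE capture incomplete and the comparison of AE rates unreliable.

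No numerical size is given, because the article states no MACCE or AE rates and any figure would be invented. The reach is limited: these are secondary and safety outcomes in a pilot of 60 patients, 30 per group, whose primary outcome is slow flow/no-reflow. The AE conclusion assumes that the definition is applied literally. If staff already record all untoward events, the defect is one of wording. A claim that MACCE favors one arm is not supported.

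**What to change.** **MACCE (section 2.9.2, item 7).** Add stroke to the components. Report each component separately as well as the composite, so that hemorrhage and readmission can be seen apart from the rest. Report all-cause death alongside.

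**AEs (section 2.11).** Define an AE as any untoward event from randomization to one month in either arm, whether or not it is expected and whatever its cause. Record expectedness and relationship to EA as two separate fields. Tabulate needle-site reactions as EA-specific reactions, and state that they are not counted as MACCE hemorrhage.

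**Cost.** New definition wording, a few case-report fields at contacts already scheduled in Table 1, and slightly more AE entries. Recruitment is ongoing and section 2.17 requires re-approval of protocol changes, so an amendment is needed, and the records of patients already enrolled should be checked against the new definitions.

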### Safety assessments

2.10

All the participants will undergo laboratory tests, including routine blood tests, levels of electrolytes, as well as liver and renal functional tests immediately after admission and three days after surgery. Treatment safety will be assessed based on these test results. Participants will provide consent for these biological samples as an addendum when they sign the informed consent form.

### Adverse events

2.11

Adverse events (AEs) are unexpected symptoms, signs, or health conditions associated with the treatment. Pre-existing health conditions or diseases will be categorized as AEs only if they worsen post-treatment. Abnormal laboratory tests will be considered as AEs if they represent clinically significant symptoms that require treatment. Common adverse reactions to electroacupuncture include broken needles, fainting, bleeding, bruising, infection, swelling, and other discomforts following needle insertion such as post-acupuncture pain, nausea, palpitations, dizziness, headache, and insomnia. Detailed AE data will describe the symptoms, severity, onset date, relationship with study manipulation, measures taken in response (including drug combination, dosage, start and end times), intervention methods (such as ceasing acupuncture), duration, follow-up, and outcomes. Follow-up will be conducted immediately after enrolment, and timely reports will be submitted to the principal investigator until all the issues are resolved. The investigator has the authority to determine trial termination and provide economic compensation for study-related harm. Loss of follow-up will also be recorded if the investigator cannot obtain information regarding adverse events.

Serious Adverse Events (e.g., resulting in death, hospitalization, or disability) will be promptly reported to the principal investigator and the Medical Ethics Committee. The Case Report Form (CRF) will document the time of death and autopsy results, if applicable.

### Calculation of sample size

2.12

Since previous RCTs have not investigated acupuncture as an adjunct intervention for managing SF-NR in the AMI patients during PCI, it is challenging to determine the optimal sample size through power calculation. Therefore, instead of a formal sample size estimation, this trial will use a preliminary exploratory clinical pilot design for estimating the sample size (47). However, to preliminarily assess the feasibility of acupuncture-assisted PCI to prevent SF-NR, we will meticulously ensure adequate number of participants in our experimental design by adhering to the established guideline of a minimum of 12 participants per group for pilot studies (48). A previous study suggested that each group should have a sample size ranging from 20 to 25 cases for exploratory clinical trials assessing the effectiveness of intervention measures (49). Therefore, in this study, each group consisted of 25 patients and a total of 50 cases for the 2 groups. However, to account for a dropout rate of 20%, this study will recruit 60 patients (30 patients per group). It seems plausible that the dropout rate would be less than 20% because of the short duration of the procedure and the high requirement of surgery among the participants (50). The results of this study will contribute to providing the effect size data for calculating sample sizes in the further large-scale RCTs.

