### Study design

2.1

This pilot trial will adopt a single-center, blinded, randomized controlled design to determine the efficacy of intraoperative EA in preventing or reducing the incidence of SF-NR in patients with AMI undergoing PCI with standard PCI as control. The trial will follow the Chinese AMI management guidelines and the Declaration of Helsinki. This study has been approved by the Ethics Committee [Approval No. 2023-090-01]. All the study participants will be screened according to the inclusion and exclusion criteria. Finally, sixty eligible patients will be recruited and randomly assigned in a 1:1 ratio to either the EA group or the control group after obtaining informed consent. Patients in the acupuncture group will receive electroacupuncture during the standard PCI procedure, whereas patients in the control group will only receive the standard PCI procedure. The trial period will include the treatment duration from the time of hospital admission to the completion of PCI and a one-month follow-up period.

The protocol will be designed in compliance with the Standard Protocol Items for Randomized Trials (SPIRIT). The SPIRIT checklist is included in the Supplementary Appendix. The trial flow chart is shown in Figure 1. The study design schedule is shown in Table 1.

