### Statistical analysis

2.15

Statistical analysis will be performed according to the intention-to-treat (ITT) principle using the SPSS V.25.0 software (IBM Corporation, Armonk, New York, USA). Missing data will be addressed through multiple imputations. *P* < 0.05 will be considered as a statistically significant difference between groups. The normally distributed data will be presented as Mean ± SEM. The inter-group comparisons for this data will be performed using the independent sample t-tests and paired t-tests will be used within-group comparisons. Non-normally distributed data will be presented as median (interquartile range) and the independent sample non-parametric tests will be performed for comparing the data between group. Count data will be expressed as frequency (percentage) and analyzed using the chi-square test. Ridit analysis or rank sum tests will be used to assess the ordinal data.

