This study aims to confirm the efficacy of acupuncture as an adjunct to standard AMI therapy with strict quality control. However, there are few limitations. Firstly, conducting a fully randomized placebo-controlled acupuncture trial is challenging because of the nature of electroacupuncture intervention. To overcome this, we will implement a series of measures to minimize the single-blind bias as much as possible. We have meticulously designed our trial and adhering to methodological standards for allocation concealment and blinding will enhance the generalizability of our findings. To avoid unwarranted interference or risk to AMI patients through sham needling and focus more closely on studying the effects of acupuncture, this pilot study will use a non-acupuncture control group and implement blinding for the outcome evaluators and statisticians to minimize bias. Secondly, cardiac magnetic resonance (CMR) is considered the preferred method for assessing microvascular damage and offers benefits in the assessment of myocardial perfusion and cardiac function (67). In future clinical trials, the potential utilization of CMR for evaluating the cardioprotective effects of acupuncture will be explored. Thirdly, because of the financial and workforce constraints, this trial is not a multi-center study. This would result in a small sample size and therefore, the results may be potentially influenced by the geographical factors. Therefore, larger multi-center RCTs will be necessary to validate the results of this pilot trial. Finally, the pathophysiological mechanisms involved in coronary microvascular dysfunction, injury, and obstruction include microembolization, edema/capillary obstruction, RBC stasis, capillary rupture, leukocyte adhesion, and impaired vasomotion (68–70). However, the precise myocardial protective mechanisms of acupuncture remain ambiguous. We will intend to seek approval from the ethics committee to retain blood samples from patients both pre- and post-treatment, with the goal of investigating relevant plasma biomarkers to elucidate the therapeutic mechanisms of EA.

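### Sixty recruits less 20% dropout leave 24 per arm, not 25; and the article's language of confirming efficacy does not fit its unpowered exploratory design

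*Protocol article*

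**What the plan says.** Section 2.12 (Calculation of sample size) gives up a power calculation: "instead of a formal sample size estimation, this trial will use a preliminary exploratory clinical pilot design for estimating the sample size". It takes its size from a rule of thumb that "each group should have a sample size ranging from 20 to 25 cases for exploratory clinical trials", and settles on the upper end: "each group consisted of 25 patients and a total of 50 cases for the 2 groups". It then inflates for loss: "However, to account for a dropout rate of 20%, this study will recruit 60 patients (30 patients per group". The next sentence expects the loss to be smaller: "It seems plausible that the dropout rate would be less than 20" percent. The section ends by saying that the results will supply effect-size data for larger trials.

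Section 2.15 (Statistical analysis) assigns the chi-square test to count data and says that P below 0.05 "will be considered as a statistically significant difference between groups". Analysis is by intention to treat, with multiple imputation for missing data.

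The Discussion (section 3) says: "This study aims to confirm the efficacy of acupuncture as an adjunct to standard AMI therapy with strict quality control". Its closing paragraph, and the Discussion part of the Abstract, say that if the treatment is shown to work it will supply a new strategy against SF-NR.

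**The concern.** There are two separate faults.

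The first is arithmetic. The recruited number is presented as protecting 25 per group against 20% dropout. It does not, because the 20% was added to the evaluable target instead of being taken off the recruited number.

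The second is a mismatch of purpose. A design sized by a rule of thumb, with no effect size and no power, can estimate a difference with wide uncertainty. It is not built to confirm efficacy. If the confirming language carries through to the report, a non-significant result may be taken as absence of effect, and a significant one as more settled than it is. Section 2.12 also means to pass the estimate on to later trials, so its uncertainty needs to be visible.

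**Working it through.** **Inputs.** From section 2.12: target 25 per arm, 50 in total; dropout d = 0.20; recruited 60, 30 per arm. From section 2.1 (Study design): patients are "randomly assigned in a 1:1 ratio to either the EA group or the control group", so losses are taken as equal between arms.

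**1. Reproduce the plan's figure.** n × (1 + d): 25 × 1.2 = 30 per arm; 50 × 1.2 = 60 in total. This matches the article exactly.

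**2. Correct inflation.** n / (1 − d): 25/0.8 = 31.25, rounded up to 32 per arm (64 in total); on the total alone, 50/0.8 = 62.5, rounded up to 63.

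**3. What 60 delivers.** 60 × (1 − 0.20) = 48, or 24 per arm. The loss at which 50 remain is 1 − 50/60 = 16.7%.

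**4. What the design can show (illustration only).** The article gives no effect size. Assumptions made here: control rate 41% (the one SF-NR rate in the article, a background figure in the Introduction), a halving to 20.5%, and a two-sided 0.05 level (the article does not state sidedness).

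Power was found by summing the two binomial probabilities over all pairs of event counts for which the uncorrected chi-square test gives P < 0.05. The half-width of the 95% confidence interval for the risk difference is 1.96 × √[(0.41 × 0.59 + 0.205 × 0.795)/n] = 1.96 × √(0.404875/n).

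| Per arm | Exact chi-square power | 95% CI half-width |
|---|---|---|
| 24 | 34.3% | 25.5 points |
| 25 | 36.3% | 24.9 points |
| 30 | 40.4% | 22.8 points |

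With a normal approximation and 30 per arm, 80% power needs a fall from 41% to about 10%. With the same approximation, control rates of 10%, 20% and 30% give power to detect a halving of about 10 to 11%, 16 to 19% and 23 to 28% over 24 to 30 per arm.

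**5. Purpose against design.** Section 2.12 describes an exploratory pilot with no formal sizing, meant to feed later trials. The Discussion states an aim of confirming efficacy, and both its close and the Abstract speak of the treatment being proven. These descriptions do not agree.

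**The case against.** **On the arithmetic.** The 25 is not a power or precision requirement. It is the top of a 20 to 25 range, and 24 is still inside it and twice the minimum of 12 per group that section 2.12 also cites. The article expects loss below 20%. The primary outcome is assessed immediately after stent implantation (section 2.9.1), so loss during the one-month follow-up does not remove it, and the analysis is by intention to treat. All of this stands and makes the slip minor. Some withdrawals listed in section 2.5 could occur before or during treatment, so primary-outcome loss need not be zero. An expectation of lower dropout also does not make the stated 20% allowance correct.

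**On purpose.** The Discussion itself lists the small sample as a limitation and says that larger trials at several centres must validate the results. That tempers the confirming language but does not remove it, and the two statements sit in the same paragraph.

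**Stronger readings that a reader might infer.** One is that the article says efficacy is confirmed if P < 0.05. It does not: section 2.15 only labels such a result statistically significant, and no sentence turns that into a rule for declaring efficacy. Another is that the trial misses a promised power. None is promised; section 2.12 openly forgoes the calculation, and the power figures above rest on assumed rates. A third is that the primary analysis will fall below 25 per arm. With the outcome read in the procedure, it may well stay near 30.

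**Conclusion.** The dropout inflation is wrong as written: at the stated 20% loss, 60 recruits give 24 per arm, one short of the stated 25 in each arm, and 25 holds only up to 16.7% loss. The missing patient matters little. Under the illustrative rates, going from 25 to 24 per arm lowers power from 36.3% to 34.3% and widens the interval by about half a point on each side.

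The weightier part is the wording. An aim to confirm efficacy, and talk of the treatment being proven, do not fit a design that the article itself calls exploratory and leaves unpowered. Intervals of roughly ±23 to 25 points show why, on the assumption of a 41% control rate and a halving. This is an inconsistency in the stated aims. It is not evidence that the article sets a P-value rule for efficacy.

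**What to change.** - **Section 2.12:** keep 60 and restate what it covers, either up to 16.7% loss with 25 per arm kept, or 24 per arm at 20% loss. Add that the primary outcome is read during the procedure, so most randomised patients should contribute to it.
- **Abstract and Discussion:** replace the language of confirming and proving efficacy with estimation, that is, estimating the difference in SF-NR incidence to inform a larger trial.
- **Section 2.15:** report the SF-NR risk difference with a 95% confidence interval beside the chi-square P-value, and say that the P-value is exploratory.

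The cost is a few sentences and one confidence interval. The stated dropout cover becomes slightly less favourable. Enrolment, procedures and data collection do not change, so this can be done while recruitment is under way.
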